***Tertiary outcomes***		
Outcome 14	ACNs diagnostic accuracy for conducting FLUS compared with a FLUS-specialist	ACNs conclusions are index test and FLUS-specialist conclusions used as reference test

*ACNs* Acute community Nurses, *ACHCS* Acute Community Health Care Service, *FLUS* Focused Lung Ultrasound, *PCP* Primary Care Physician

^a^Day 0: Defined by Day of inclusion

### Data collection

During the in-home assessment participants will undergo a systematic screening and examination program, which include registration of age, gender, alcohol consumption, smoking, BMI, nationality, comorbidity, polypharmacy, place of assessment, symptoms of infection, days with symptoms, Clinical Frailty Scale [45], vital signs (blood pressure, pulse, oxygen saturation, respiratory frequency, and ear temperature), and POCT for analyses of CRP and haemoglobin.

In addition, the intervention group will undergo the extended POCT examinations (FLUS and biochemistry on blood analysis).

Outcomes for the 30 days-follow up period are collected from electronic databases. Table 2 provides an overview of the data-sources and corresponding time-points for each outcome.

**Table 2 Tab2:** Time point and data-sources for primary and secondary outcomes

	**Day 0**^**a**^			**Follow up: 30 days**			
	**During in-home assessment**	**ESCR**	**Danish health registries**	**ESCR**	**EPJ**	**FMK**	**Danish health registries**
**Primary outcome**							
Hospital admission	x		x		x		x
**Secondary outcomes**							
Readmission					x		x
Death					x		x
Hospital-free days							x
Length of hospital stay					x		x
Complications during hospital stay					x		
Treatment initiations	x					x	x
Treatment changes						x	x
Amount of home care		x		x			
Re-referral to ACHCS				x			
Contact to PCP			x				x
*Data collector*	*ACN*	*Nexus administrator*	*Primary investigator*	*Nexus administrator and ACNs*	*Primary investigator*	*Primary investigator and ACNs*	*Primary investigator*

*ESCR* Electronic social care record, *EPJ* Electronic patient journal, *FMK* Medical chart (Fælles medicinkort)

^a^Day 0: Defined by Day of inclusion

### User perspectives

User perspectives on the intervention will be explored during the RCT. PCPs, ACNs, and participants will be invited to focus group interviews. Qualitative data from the user perspectives will be reported in a separate article.

### Advisory board

An advisory board, comprised of PCPs, ACNs, hospital physicians, and researchers, has been formed. The Advisory Board actively participated in the development of the working algorithm and provides support for fostering collaboration between health care providers in both the primary and secondary sector throughout the trial.

### Data sources

We will apply for access to external data sources to assess co-morbidity, disabilities, utilization of primary care and health care services, death, and medical history.

The Danish Health Data Authority is responsible for the national health registers containing health data related to all Danish citizens [46, 47]. A unique personal identification number for all people living in Denmark makes it possible to link data across national health registers. Approval granted August 2023.

The Danish Health Data Authority will be applied to get access to the Danish National Patient Registry, the Cause of Death Register, The Register of Pharmaceutical Sales, and the Danish National Health Service Register. The registers contain information about diagnoses, treatments, deaths, and health care utilization, and are needed to access information on comorbidity, time of death, medical history, treatment initiations or changes, and number of consultations at PCPs.

The Medical Chart (FMK: Fælles MedicinKort), will be applied to access register polypharmacy and type of medications. Data on amount and type of medication will be obtained at day 0 by the primary investigator. Treatment initiations or changes within 30 days follow-up (Day 1 to day 30) will be obtained by the primary investigator on Day 30. Approval granted October 2022.

The Municipal journal record, Electronic Social Care Record (ESCR), registers home care, and data will be obtained at day 1 and at day 30 to investigate possible changes as a proxy of changes in functional level. Approval granted October 2022.

The hospital journal record, EPJ will be accessed by the primary investigator to register admissions, reason for admission, and complications during admission. EPJ will be accessed at day 30 after the acute visit. Approval granted October 2022.

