### Study participants

Participants eligible for this study are people aged 65 years or older, referred to the ACHCS in Kolding Municipality for an in-home assessment.

The participants must have at least one of following symptoms of respiratory disease: cough, dyspnoea, fever, fall, or recent functional decline, defined as subjective (not able to perform normal daily activities as usual) or objective functional decline (increased need of home care). Falls and functional decline are not directly symptoms of respiratory disease, but are known as vague and atypical disease presentation; which is why we included them as signs of potential respiratory disease [31, 32].

Participants with known moderate to severe cognitive impairment are excluded from the study due to Danish legislation and the Regional Committees on Health Research Ethics for Southern Denmark.

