### Recruitment and enrolment

Patients referred to the ACHCS are visited by an ACN in their own dwelling, which may include a private house, care-home, or rehabilitation centre. If the patient fulfils the inclusion criteria, the ACN provides comprehensive information about the study both orally and in writing. Subsequently, the patient is given the opportunity to sign the informed consent document. Additional files 1 and 2 contain details pertaining to the informed consent process and written participant information. These documents have received approval from the Regional Committees on Health Research Ethics for Southern Denmark.

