***Secondary outcomes***		
Outcome 2	Hospital admissions at Day 0^a^	Proportion of hospital admission at Day 0^a^
Outcome 3	Readmission ≤ 30 days	Proportion of readmissions within 30 days follow-up (Day 1 to Day 30)
Outcome 4	Mortality ≤ 30 days	Number of deaths within 30 days follow-up (Day 0^a^ to Day 30)
Outcome 5	Length of hospital admission	Number of days admitted
Outcome 6	Hospital-free days ≤ 30 days	Number of days alive that is spend outside of an acute-care hospital, long-term acute-care hospital or in an emergency department. Days spent wholly or in part under “observation” status counts as hospital days [44]
Outcome 7	Complications during hospital admission	Number of complications during admission, registered in the electronic patient journal
Outcome 8	Treatment initiations or changes at Day 0^a^	Number of treatment initiations or changes at Day 0^a^
Outcome 9	Treatment initiation or changes ≤ 30 day	Number of treatment initiations or changes within 30 days follow-up (Day 1 to Day 30)
Outcome 10	Functional level	Proxy assessment of functional level: - Change in amount of home care within 30 days follow-up - Number of changes of dwelling
Outcome 11	Re-referrals to the ACHCS	Number of re-referrals to the ACHCS
Outcome 12	Contact to the PCP ≤ 30 days	Number of contacts to the PCP within 30 days follow-up (Day 0^a^ to Day 30)

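### Outcome 10's first home-care reading is set at day 1 in the text but Day 0 in Table 2; a day-1 baseline would follow the intervention

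*Protocol article*

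**What the plan says.** Table 1 of the protocol article lists functional level as Outcome 10, assessed by proxy through two components: "Change in amount of home care within 30 days follow-up - Number of changes of dwelling".

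The article gives the timing of the first home-care reading twice:

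- **Data sources**, on the municipal record (ESCR): "data will be obtained at day 1 and at day 30 to investigate possible changes as a proxy of changes in functional level".
- **Table 2** ("Time point and data-sources for primary and secondary outcomes"): the row "Amount of home care" has one mark in the ESCR column under Day 0 and one in the ESCR column under the 30-day follow-up. The footnote reads "Day 0: Defined by Day of inclusion".

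The Study participants section shows which direction counts as worse. Its inclusion criterion describes "objective functional decline (increased need of home care" as one form of recent decline.

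The Statistical analyses section lists amount of home care among the baseline characteristics. Its adjustment set (gender, age, civil status, co-morbidity, alcohol, smoking, living alone, BMI) does not include it.

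**The concern.** A change score needs a starting value that allocation cannot have touched. Consent, randomisation and the in-home assessment all belong to Day 0, and the results then go to the primary care physician. Admission on that same day is counted as Outcome 2. A home-care value that refers to day 1 comes after all of this. If care was stepped up as a result of the visit, or suspended because the person was admitted, the reading already contains part of the trial's effect.

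Outcome 10 is the only outcome in Table 1 labelled as functional level, and the Key limitations section concedes that there are no patient-reported outcomes. The Background expects earlier diagnosis to prevent functional decline, so the measure most directly tied to that expectation should have a clean baseline.

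A related point concerns day 30. Because more home care stands for decline, a fall in recorded home care is naturally read as the favourable direction. That reading makes no sense for someone who has died, is in hospital or has newly entered a care home.

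**Working it through.** The article gives no figure for Outcome 10, so there is none to reproduce. Its sample size concerns 30-day admission only. The pooled, two-sided formula without continuity correction gives [1.96 × √(2 × 0.26 × 0.74) + 0.8416 × √(0.31 × 0.69 + 0.21 × 0.79)]² / 0.10² = 300.8. Rounded up, this is 301 per arm and 602 in total, as stated. Nothing below changes it.

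**Step 1: what day 1 means in this article.** In Table 1, readmissions (Outcome 3) and later treatment changes (Outcome 9) are counted from Day 1, while treatment changes at the visit (Outcome 8) belong to Day 0. The Data sources section likewise takes medication at day 0 and treats Day 1 to day 30 as follow-up. In the article's own usage, Day 1 is the first day after the visit.

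**Step 2: whether Day 0 settles it.** Not fully. Day 0 is the day of inclusion, so it contains both the hours before the visit and everything that follows on that day. Neither place fixes a value from before the intervention.

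**Step 3: how a day-1 baseline enters the comparison.** Write:

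- B = home care in force before the visit
- H1 = B + s = home care at day 1, where s is any shift caused by Day 0 events
- H30 = home care at day 30

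The measured change is H30 − H1 = (H30 − B) − s. Taking intervention minus control:

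measured difference = difference from the pre-visit baseline − (mean s in intervention − mean s in control)

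If a Day 0 event occurs in a share p of an arm and shifts recorded home care by d on average, with the same d in both arms, the error term is −d × (p_int − p_ctrl).

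- It is zero if the arms have equal Day 0 event rates, or if the event leaves the record unchanged (d = 0).
- If admission lowers recorded home care (d < 0) and the intervention reduces Day 0 admissions, the error is negative. Control then appears to gain more home care, which favours the intervention.
- If the intervention raises Day 0 admissions, which the Discussion accepts as possible, the sign reverses.

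Adjusting for H1 as a covariate would not cure this, because H1 is itself measured after randomisation.

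**Step 4: size.** The formula needs d and both Day 0 event rates. The article gives no home-care hours and no expected Day 0 admission rates; its 31% and 21% refer to 30-day admission. It does not say whether the ESCR holds allocated or delivered care, or whether an entry falls during a hospital stay. No magnitude can be derived.

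**The case against.** The strongest reply is that day 1 may be only the date of extraction. The same section says that treatment changes over Day 1 to day 30 are obtained on Day 30, so the verb can describe when the record is read rather than the date to which the value refers. Table 2 assigns the Day 0 ESCR column to the Nexus administrator, which would fit a next-day extract of the Day 0 value. This stands as a possible reading, and it means that a post-intervention baseline is not established. It does not remove the conflict between the two places, and it still leaves no value stated to be from before the visit.

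A reader might go further and infer that the plan scores death, hospital stay or a care-home move as improved function. The documents do not support that. No section codes these states as zero home care or as improvement. Changes of dwelling are a separate component of Outcome 10, and deaths, length of stay and hospital-free days are separate outcomes. The Statistical analyses section restricts analysis to participants with available outcome data and foresees imputation and sensitivity analyses, so a participant who died could equally be treated as missing. Detailed handling may sit in an analysis plan that is not shown.

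Enrolment sites, "which may include a private house, care-home, or rehabilitation centre", might also suggest that some participants have no usable home-care value, but the article does not say what the record holds for them.

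**Conclusion.** The conflict between the Data sources section and Table 2 is real and should be resolved. If the Data sources wording is followed literally, Outcome 10 starts from a value taken after randomisation, the intervention and any Day 0 admission. Bias between arms then follows only if the arms differ in Day 0 events that alter recorded home care; its direction could go either way and its size is unknown. If day 1 is merely an extraction date, the remedy is a clarification of wording.

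On the states at day 30, the supportable statement is limited. Home care is a proxy in which increased need means decline, so absence of home care because of death, hospital stay or a new care-home placement should not be counted as a reduction. This is a safeguard to write down, not an error in a stated scoring rule.

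The point touches one component of one secondary outcome. The primary outcome and the sample size stand.

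**What to change.** 1. Reconcile the Data sources section with Table 2, and state separately the date on which the record is read and the date to which the value refers.
2. Define baseline as the home-care allocation in force immediately before the Day 0 visit, in both arms. Use the same value in the table of baseline characteristics.
3. Analyse day-30 home care with that baseline as a covariate; it is absent from the present adjustment set.
4. State that participants who are dead, in hospital or newly in a care home at day 30 are not counted as having reduced home care, and report the number in each state by arm beside the home-care result.

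The cost is a reference date in the record extract and a few lines of text. This assumes that the municipal record shows the allocation by date, which the article does not say. Inclusion was expected to end on 31 August 2023, before the article appeared, so retrospective availability needs to be confirmed. If the pre-visit value cannot be recovered, the report should say that the baseline is post-randomisation and show Day 0 admissions by arm next to Outcome 10.

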### Data management

#### Data documentation

The project is registered with the Research & Innovation Organization (RIO), University of Southern Denmark, record of data processing activities, (Project identification number: 11.404). Data will be processed and stored in accordance with EU General Data Protection Regulation (GDPR) and the Danish Data Protection Act.

Collected data will be stored in the Open Patient Data Exploratory Network (OPEN). OPEN delivers expertise in collection, registration, and documentation of data that meets the rules of protection of personal data. All data will be stored and entered using REDCap® [34, 35].

### Data monitoring

Mortality rates will serve as a safety assessment and will be checked monthly to ensure that mortality is not increased in the intervention group. A data monitoring committee has not been established for this trial as the trial has minimal risk (see Additional file 1).

To ensure adherence to protocol, we will monitor number of biochemistry kits used and logging data from all POCT devices.

### Data analyses

#### Sample size and statistical power

A parallel group design with a 1:1 allocation ratio and a superiority design was chosen for this trial. To our knowledge, the number of patients acutely admitted after a visit from ACNs are unknown. Preliminary results from a pilot-study of the intervention (not yet published) showed that 21% of included participants were acutely admitted after a visit from ACNs. We aimed to detect a clinically significant absolute reduction in acute hospital admission of 10%. Therefore, based on data from the unpublished pilot-study, we aimed in detecting a reduction from 31 to 21% at a significance level 0.05 with a power of 0.80, requiring a total of 602 participants (301 in each arm). Allowing for a 5% dropout after randomisation, 316 in each arm are required (a total of 632 participants).

### Statistical analyses

Statistical analysis will be carried out using STATA® (StataCorp LLC, Texas, USA).

Data analysis will be conducted according to intention to-treat principles and include all eligible participants with available outcome data. Missing data will be reported for each variables, including reasons. Imputation and sensitivity analysis will be used to assess the potential biases caused by missing outcome data.

Descriptive statistics for both groups will be summarised including demographic and baseline characteristics: patient symptoms, referring health professional, Clinical Frailty Scale (CFS) [45, 48], co-morbidities, daily medication, amount of home care, alcohol consumption, smoking, BMI, vital signs (blood pressure, pulse, oxygen saturation, respiratory frequency, and ear temperature), treatment initiations or changes, admissions, re-referrals to the ACNs, contacts to the PCPs, and mortality.

In the intervention group, descriptive statistics will also include POCT measurements and FLUS findings.

Categorical data will be reported as numbers and percentages. Continuous data will be presented as means (SD) on normally distributed data and medians [IQR] with range on non-normally distributed data. Differences in baseline characteristics between the intervention group and control group will be calculated using Chi-squared test, Fischer’s exact test, and Wilcoxon-Mann–Whitney test as appropriate. The statistical significance threshold for all tests is *p* < 0.05.

For the primary outcome univariate and multivariate logistics regression models will be used to investigate risk of admission between groups.

Univariate and multivariate logistic regression models will be used to compare secondary outcomes between the two groups.

Both regression models will be adjusted for possible confounders (gender, age, civil status, co-morbidity, alcohol consumption, smoking, living alone, and BMI).

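### Hospital-free days (Outcome 6): at the plan's own admission rates the median sits at its maximum in both arms, and nothing else in the plan estimates days saved

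*Protocol article*

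**What the plan says.** Three parts of the protocol article bear on this.

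- **Summary rule** (Statistical analyses): "Continuous data will be presented as means (SD) on normally distributed data and medians [IQR] with range on non-normally distributed data". The choice depends on the shape of the distribution, not on what the figure is meant to show.
- **Outcome** (Table 1, Outcome 6): hospital-free days within 30 days, defined as "Number of days alive that is spend outside of an acute-care hospital, long-term acute-care hospital or in an emergency department". Days under observation status, even in part, count as hospital days.
- **Planning rates** (Sample size and statistical power): "we aimed in detecting a reduction from 31 to 21% at a significance level 0.05 with a power of 0.80", for the proportion admitted.

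The arms are compared on secondary outcomes by univariate and multivariate logistic regression. Hospital-free days is not named in the list of variables to be described, but as a skewed day count it falls under the general rule.

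**The concern.** A participant who survives and never enters hospital scores the maximum. If more than half of an arm does so, its median is the maximum, however many days the rest spend in hospital. Two arms in that position have the same median whatever the treatment does to admissions or to length of stay.

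This matters because the article expects more than fewer admissions. The Background hypothesises an effect on length of stay, and the Discussion section on over-diagnosing and over-treatment allows that admissions might even rise while time in hospital improves. Hospital-free days can capture that for every randomised participant. With equal medians and an odds ratio, a reader could take the outcome as showing no difference, and would have no estimate of days gained per participant.

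**Working it through.** **Inputs from the article:** 31% v 21% admitted, alpha 0.05, power 0.80, 301 per arm before dropout.
**Assumed, because the article gives no figures:** mean hospital days per admitted participant L = 3 to 10; deaths among the non-admitted d = 0, 5 or 10%; a maximum of 30 days (31 would not change the result).

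**1. The plan's own figure.** Two-sided test of two proportions, pooled variance under the null, no continuity correction, mean proportion 0.26:

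n = [1.960 × √(2 × 0.26 × 0.74) + 0.842 × √(0.31 × 0.69 + 0.21 × 0.79)]² / 0.10² = (1.216 + 0.519)² / 0.01 ≈ 301 per arm.

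The stated 301 is reproduced, so the planning rates are taken as they stand.

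**2. Position of the median.** Never admitted: 1 − 0.31 = 0.69 and 1 − 0.21 = 0.79, both well above 0.50. The binomial probability that at least 151 of 301 are admitted is 3.5 × 10⁻¹² at 31% and 5 × 10⁻²⁹ at 21%.

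**3. What would move it.** Non-admitted participants also fall below the maximum if they die or have an emergency department contact or observation day without admission. For the control median to drop, this would have to affect more than (0.50 − 0.31)/0.69 = 27.5% of non-admitted controls. In the intervention arm the figure is (0.50 − 0.21)/0.79 = 36.7%.

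**4. Lower quartile.** The two planning rates lie on either side of 25%. The probability that at least 76 of 301 are admitted is 0.988 in control and 0.043 in intervention, so the control quartile is expected below the maximum and the intervention quartile at it.

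**5. Mean difference.** With no deaths outside hospital it is (0.31 − 0.21) × L = 0.10 × L: 0.3, 0.5, 0.7 and 1.0 days for L = 3, 5, 7 and 10.

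Simulation with 301 per arm, 2,000 trials per setting:

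| Mean stay L | Deaths d | Both medians at maximum | Control quartile lower | Mean difference (days) |
|---|---|---|---|---|
| 3 | 0 | 100% | 95% | 0.30 |
| 3 | 5% | 100% | 67% | 0.21 |
| 3 | 10% | 100% | 75% | 0.13 |
| 5 | 0 | 100% | 97% | 0.50 |
| 5 | 5% | 100% | 93% | 0.42 |
| 5 | 10% | 100% | 85% | 0.34 |
| 7 | 0 | 100% | 97% | 0.69 |
| 7 | 5% | 100% | 95% | 0.60 |
| 7 | 10% | 100% | 90% | 0.54 |
| 10 | 0 | 100% | 99% | 0.96 |
| 10 | 5% | 100% | 97% | 0.89 |
| 10 | 10% | 100% | 92% | 0.77 |

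The difference shrinks as d rises because the same death rate is applied to the non-admitted of both arms, and the intervention arm has more of them.

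**6. What the quartile measures.** With 31% admitted and no deaths outside hospital, the lower quartile is reached after counting 25/31 of the admitted, from the longest stay down. It is therefore set by about the shortest fifth of stays (6/31 = 19%). Suppose 31% were admitted in both arms and mean stay fell from 7 to 5 days. The mean would rise by 0.31 × 2 = 0.62 days, both medians would stay at the maximum, and the quartile would depend only on how short stays changed.

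**The case against.** **The rule gives more than a median.** It asks for the IQR and range too, and at exactly 31% v 21% the lower quartile would usually differ. This stands. It would therefore be wrong to infer that the planned effect cannot show in the plan's summaries. But the quartile separates the arms because the planning rates straddle 25%, and the article itself says the admission rate after these visits is unknown. If both true rates were below 25%, with few deaths outside hospital, both quartiles would also sit at the maximum. In either case the quartile does not measure days saved.

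**The sentence is descriptive; the arms are compared by logistic regression.** Also true, so identical medians are not the plan's test result. But an odds ratio carries no information in days, so the median [IQR] with range remains the only day-scale summary stated. A separate analysis plan may add to this. The point here is limited to what the article fixes.

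**The planned effect is on another outcome.** The 10-point reduction concerns the proportion admitted, which is reported as numbers and percentages. A reader might infer that a successful trial would look null; the article does not support that.

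**Length of stay is its own outcome.** Outcome 5 counts days admitted without naming a denominator. Over all randomised participants its median would be zero in both arms for the same reason. Over admitted participants only, it compares groups formed after randomisation.

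**Other counts.** It is tempting to extend the point to complications, re-referrals and changes of dwelling. The article gives no rates for the last two, and complications may be meant for admitted participants only. The extension is therefore conditional.

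**Conclusion.** The point holds for hospital-free days, a secondary outcome. At the plan's own rates the median is the maximum in both arms and cannot separate them, while the means differ by about 0.3 to 1.0 days per participant with no deaths outside hospital and about 0.1 to 0.9 days with 5 to 10% such deaths. The primary outcome and its analysis are untouched.

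The result for the median assumes that 31% and 21% apply over the 30-day window, and that fewer than 27.5% of non-admitted controls lose days through death, emergency department contact or observation. The size of the mean difference rests on assumed stays and deaths, and is illustrative. This is a cheap improvement to reporting, not a flaw that threatens the trial's main conclusion.

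**What to change.** Add a sentence to Statistical analyses. For Outcome 6, whatever the distribution, report the mean hospital-free days per randomised participant in each arm, the difference in means with a bootstrap 95% CI (resampling within arm), and the proportion at the maximum; keep the median [IQR] and range as a supplement. Do the same for other count outcomes, with the proportion at zero, only where more than half of participants turn out to be at zero.

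The cost is that sentence and a short bootstrap run, with no new data and no change to trial conduct. The small downside is that means of skewed data are sensitive to a few long stays or early deaths; the bootstrap interval reflects this, and the median [IQR] and range beside it let the reader see it.

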Point-of-care ultrasound (POCUS) has become a diagnostic tool for acute respiratory diseases over the last couple of decades. Studies have shown, that in the hands of a trained health-professional, focused lung ultrasound (FLUS), is an accurate tool for diagnosing pulmonary oedema, pneumothorax, pleural effusion, and pneumonia in emergency departments and intensive care units. [23–25]. However, there is no knowledge about its use and effects on the diagnostic process during in-home assessments. Only few studies have investigated FLUS as a diagnostic tool for pneumonia in primary care, but these studies were not representative for the geriatric population [26, 27].

The objective of this trial is to investigate whether extended POCT, including FLUS and bedside blood analysis, during in-home assessments among older adults with signs of potential acute respiratory disease, reduces hospital admission. Our primary hypothesis is that implementation of extended POCT in this context will result in a reduction in hospital admissions within 30 days compared to individuals receiving usual care, constituting our primary outcome. Additionally, we anticipate that the extended POCT will improve the accuracy and timeliness of bedside diagnostics, leading to enhanced clinical decision-making by primary care physician – reflecting our secondary outcomes and tertiary outcomes. Finally, we hypothesize that the intervention will lead to earlier identification of conditions and diseases, subsequently influencing factors such as hospital length of stay, amount of home care, and functional status during the 30 days follow up. This early diagnosis is expected to prevent functional decline, aligning with our secondary outcomes.

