### Over-diagnosing and over-treatment

We hypothesize that extended POCT improves the bedside diagnostic process and qualifies PCPs’ clinical decision-making on treatment, thereby reducing hospital admissions. However, the intervention could lead to an increase in hospital admissions by identifying conditions and diseases requiring further investigations or therapeutic treatment at hospital. We believe that by identifying conditions and diseases earlier, factors such as hospital length of stay, amount of home care, and functional status can be positively influenced during the 30 days follow up, as the patients are admitted prior to functional decline.

Any diagnostic test has false positive results, and both FLUS and bedside blood-analysis have false positive or inconclusive results that can lead to unnecessary additional treatments and hospital admissions.

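### One p < 0.05 threshold covers all 11 secondary outcomes with no adjustment, order or exploratory status, leaving a substantial chance of a false-positive secondary finding; the primary outcome's error rate is unaffected

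*Protocol article*

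**What the plan says.** The significance rule is in the protocol article, Statistical analyses: "The statistical significance threshold for all tests is" p < 0.05. The same section then states: "Univariate and multivariate logistic regression models will be used to compare secondary outcomes between the two groups". No other threshold is given for any outcome.

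Table 1 names one primary outcome (hospital admission within 30 days) and numbers the secondary outcomes 2 to 12. Outcome 10, functional level, has two measures: change in home care and changes of dwelling.

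Sample size and statistical power bases the design on the primary outcome alone, "at a significance level 0.05 with a power of 0.80".

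Two other places give the secondary outcomes inferential weight. The Background hypothesises effects on length of stay, home care and functional status, and concludes: "This early diagnosis is expected to prevent functional decline, aligning with our secondary outcomes". The Discussion, under Over-diagnosing and over-treatment, concedes that admissions could increase and then expresses the belief that "factors such as hospital length of stay, amount of home care, and functional status can be positively influenced during the 30 days follow up".

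The article contains no testing order within the secondary outcomes, no condition on the primary result, no multiplicity adjustment and no exploratory label.

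**The concern.** A single threshold for every test makes a secondary p-value below 0.05 look the same as one on the primary outcome. The 5% error rate behind the design belongs to one test; it does not cover a search across 11 or 12 measures. Several of these outcomes already have hypotheses attached, so a chance difference on one of them would arrive with an explanation ready.

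This matters most if the primary result is null or adverse. A reader could then be shown a statistically significant improvement in, say, home care, under a threshold the protocol itself set and with a mechanism the Discussion had already described. The article would give no signal that such a result is weaker evidence than the primary one.

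**Working it through.** **Step 1: the design alpha.** Inputs from Sample size and statistical power: 31% against 21%, alpha 0.05, power 0.80, 1:1 allocation. Sidedness is not stated. With two sides, pooled variance and no continuity correction, where the mean rate is (0.31 + 0.21)/2 = 0.26:

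n per arm = [1.96 × √(2 × 0.26 × 0.74) + 0.8416 × √(0.31 × 0.69 + 0.21 × 0.79)]² / 0.10²

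= [1.96 × 0.6203 + 0.8416 × 0.6163]² / 0.01 = 1.7345² / 0.01 ≈ 300.9, rounded up to 301.

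This matches the stated 301 per arm. A one-sided test would need 237. So 0.05 is two-sided and is spent on one test, the primary. The secondary tests do not alter that error rate.

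**Step 2: the number of tests.** Outcomes 2 to 12 give 11. Splitting outcome 10 into its two measures gives 12. The tertiary outcome and the baseline comparisons are not counted.

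**Step 3: false positives under independence, all nulls true.**

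- Either direction, 11 tests: 1 − 0.95^11 = 0.431. For 12: 1 − 0.95^12 = 0.460.
- Favourable direction only, 11 tests: 1 − 0.975^11 = 0.243. For 12: 1 − 0.975^12 = 0.262.
- Expected number of false positives, 11 tests: 11 × 0.05 = 0.55.

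**Step 4: allowing for correlation.** The document gives no correlations, so a range is assumed. Test statistics were simulated as Z_i = √ρ·F + √(1 − ρ)·e_i, with F and e_i independent standard normal (400,000 draws). A false positive is |Z| > 1.96 for either direction, or Z > 1.96 for the favourable one.

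| Assumed ρ | 11 tests, either | 11 tests, favourable | 12 tests, either | 12 tests, favourable |
|---|---|---|---|---|
| 0 | 0.431 | 0.243 | 0.460 | 0.262 |
| 0.3 | 0.374 | 0.191 | 0.399 | 0.202 |
| 0.5 | 0.302 | 0.151 | 0.319 | 0.160 |
| 0.8 | 0.179 | 0.089 | 0.186 | 0.093 |

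For 11 tests the either-direction figure runs from 0.179/0.05 = 3.6 times to 0.431/0.05 = 8.6 times the nominal level. The favourable-direction figures compare with 0.025 for a single test.

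**Step 5: what is not in these figures.** Each outcome is to be analysed with both univariate and multivariate models, and the article does not say which one decides. That could add to the error rate; it was not quantified.

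**The case against.** The strongest reply is that this is a condensed article. Testing order, adjustment and exploratory labels are commonly left to a full protocol or analysis plan that is not shown. The threshold sentence also closes the paragraph on baseline comparisons, and a conventional 0.05 is not in itself a claim of confirmatory status. The part about omissions is fair. But the article is not silent on the rule: it states one, applies it to all tests, and gives no other for the outcome models that follow. The point rests on that stated rule.

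Four stronger readings are tempting, and the documents do not support them.

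- A reader might infer that a false secondary finding is likely. Every figure above is below one half, and the highest, 0.46, needs 12 independent tests. Independence is implausible: Day 0 admission is part of the primary outcome, and readmission, length of stay and hospital-free days overlap.
- A reader might infer that the protocol plans to claim benefit even if admissions rise. The Discussion states a belief about three outcomes, within a passage about possible harm. It sets no decision rule and says nothing of the other outcomes.
- A reader might count 12 separate routes to a positive conclusion. No passage says a secondary result would establish effectiveness. Mortality serves as a safety check, and treatment changes and contacts with the primary care physician have no stated favourable direction. That last fact cuts both ways: where no direction is given, a difference either way could be presented as support, which moves the relevant figure towards the either-direction column.
- A reader might think the primary inference is compromised. It is not: there is one prespecified primary outcome, and Table 1 does rank primary above secondary. What is missing is any order or status within the secondary level.

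**Conclusion.** The concern holds in limited form. The protocol applies p < 0.05 to all tests, compares 11 secondary outcomes (12 measures) between arms, and attaches hypotheses to several, without adjustment, order or exploratory status. If the intervention does nothing, the chance of at least one nominally significant secondary difference among 11 tests is 43% under independence, about 30% at correlation 0.5 and 18% at 0.8; in the favourable direction, 24%, 15% and 9%. These figures assume that all 11 nulls are true, that tests are two-sided and that correlations are equal, with the correlations assumed and not taken from the document. The risk is substantial and concerns what may be concluded from secondary results, especially after a null or adverse primary.

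**What to change.** In Statistical analyses:

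1. Limit the p < 0.05 significance claim to the primary outcome.
2. State that outcomes 2 to 12 are exploratory and will be reported as effect estimates with 95% confidence intervals.
3. State that secondary differences after a null or adverse primary result are hypothesis-generating.

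No confirmatory secondary should be newly chosen now. Inclusion was expected to end on 31 August 2023 and the article appeared on 16 February 2024. The trial is open-label, and the primary investigator collects much of the outcome data, so a late choice could look post hoc. Nothing in the document ranks one secondary outcome above the others.

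The cost is a sentence or two of wording, with no new data and no further participants. The small downside is that secondary differences can no longer be reported as confirmed effects.
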